##### Module 4: (Re)lapse

The beginning of this module emphasizes how an initial lapse need not be a catastrophic event that inevitably leads to a full-blown relapse. Rather, participants are encouraged to learn from such lapses (e.g., since they might provide clues on issues that still require clarification) and, thereby, come to a clearer understanding of the path they ultimately must take to reduce their cannabis use as a long-term endeavor and learn to be patient and self-forgiving during this process. A core element of this module is its discussion of the relapse cycle: the chain of events that might lead to a (re)lapse (adapted from [31]). Hereby, the important role that thoughts play at each point in the cycle is emphasized [31] and participants are encouraged to think of personal examples. Furthermore, they are taught that slowing down and observing one’s own thoughts, emotional states, and physical reactions might create an opportunity for them to step out of the relapse cycle and their prior automatic pilot mode and arrive at a more considered response [31]. In this respect, participants are invited to use the SOBER breathing space (this time around with a particular focus on thoughts) [31].

The module also shows participants ways for them to cope with (re)lapses. Among other things, it emphasizes the importance of being self-forgiving in such situations and introduces corresponding mindfulness practices [56]. At the end of the module, the discussion’s scope is broadened again by explaining how mindfulness can be integrated into one’s everyday life and by introducing the concept of ‘walking meditation’ [60].

##### Module 5: time for yourself

In this module, participants are encouraged to take the time they need to work on their needs so they can improve their general well-being and, thereby, construct a solid foundation upon which they may reduce their cannabis consumption. How these needs might be impacted by the use of cannabis and how mindfulness (including specific mindfulness practices) might be helpful when working on these needs are illustrated. More specifically, participants learn how to (1) improve the way they deal with stress (e.g., by first stopping and becoming aware of what happens in stressful situations, so they can learn to respond in a more considered and less automatic manner) [32], (2) develop healthier sleep habits (e.g., by unwinding before getting into bed) [61, 62], (3) reduce ruminations ([61, 63–67], including the mindfulness practices ‘recognizing thoughts as thoughts’ [56] and ‘loving-kindness meditation’ [56]), and (4) strengthen their social contacts ([23]; e.g., by becoming aware of possible negative beliefs that might inhibit them from getting closer to people (the loving-kindness meditation [56] is suggested again for this purpose).

##### Module 6: addressing problems

The sixth module begins with a description of how low moods, problems, and the use of cannabis are connected and how this might ultimately create a vicious cycle [24]. Subsequently, participants learn how they can deal with both solvable and unsolvable problems. The following six-step plan is introduced to approach solvable problems: (1) define the problem; (2) define the goal that is aimed to be achieved; (3) search for possible solutions; (4) specify (small) steps to solve the problem; (5) try out possible solutions, and (6) take stock. Different techniques that might be useful for coping with unsolvable problems also are introduced (e.g., confiding in someone else or seeking contact with people with similar problems). It is also detailed how mindfulness might be of help for both solvable and unsolvable problems. Among other things, this module emphasizes that accepting ones’ feelings (including negative ones) is important. Participants also are encouraged to think about and work on their own solvable and unsolvable problems in the module.

##### Module 7: lifestyle-balance, self-care, and saying ‘no’ (refusal skills)

This module details how participants can nurture their lifestyle-balance and self-care to better achieve and maintain their consumption goal. Regarding their lifestyle-balance, participants are first asked to classify their daily activities into depleting (e.g., discouraging, exhausting, frustrating) and nourishing ones (e.g., energizing, pleasurable, satisfying; adapted from: [31]). Participants are then encouraged to plan some nourishing activities for the upcoming week and – if possible – to actively work on depleting activities (employing what they have learned in Module 6). However, it also is emphasized that this practice is not intended to eradicate all depleting activities in their life; but rather for the individual to become more aware about how their days are spent and how they might relate to certain experiences differently. Regarding self-care, participants are encouraged to develop a friendly, accepting, and benevolent attitude towards themselves and to practice the loving-kindness meditation [56]. The module also strengthens participants’ refusal skills and, by doing so, helps them to communicate clearer, more self-confidently, and less ambiguously that they no longer want to use cannabis (or not use it as often and/or as much) [15]. In this way, their risk of relapse when confronted with high-risk situations is reduced. The SOBER breathing space [31] is recommended again as a useful practice when they are confronted with high-risk situations.

##### Module 8: preserving achievements

In this final module, participants are asked to look back on the program, to visualize difficult and helpful moments, and to write down personal tips for maintaining their consumption goal. This is to prepare them for life after the program. At the end of the module, the eCoach also will point out how mindfulness was a core element of all the modules and will encourage them to continue practicing it regularly. Besides providing an overview of all mindfulness practices that were introduced in the previous modules, a list with further resources on mindfulness is provided (e.g., books, videos, courses).

#### Study arm 2: CBT-based self-help IMI

The main changes to study arm 2 in CANreduce 3.0, relative to CANreduce 2.0, can be summarized as follows. First, a tutorial has been introduced that familiarizes participants with the features of the program (see above) to increase the program’s usability. These contents have already been described in Module 1. Secondly, the order of the modules has been changed, and the first four modules must be worked through one after the other before any of the remaining four modules can be started. In contrast, users of CANreduce 2.0 were permitted to work on the modules in whatever order they chose. These changes, as well as some slight changes in the wording of the modules’ titles, have been implemented so study arms 1 and 2 in the current CANreduce 3.0 study are similar (note that the sequential order of the first four modules in the mindfulness-based study arm is necessary, as the concepts introduced in modules 1–4 build upon each other). Thirdly, some minor language and content improvements have been implemented in each module (e.g., we changed the personal pronoun from the formal "you" (German "Sie") to the informal "you" (German "Du")). Fourthly, mindfulness-related content that existed in CANreduce 2.0 has been deleted to avoid any confounding effects between the two active study arms of the current study. Lastly, the eCoach was adapted. Even though the previous study on the effectiveness of CANreduce 2.0 revealed that the study arm having an anonymous support team (and not the personal eCoach who introduced the modules via a video) was the most effective, we still used an eCoach rather than an eTeam in this study arm of CANreduce 3.0. However, since it is possible that the eCoach in CANreduce 2.0 did not match all the participants’ expectations (e.g., in terms of gender or age), the eCoach for CANreduce 3.0 is now displayed schematically (as an avatar picture) and participants can choose between either a male or female version. Furthermore, and analogous to study arm 2, the eCoach now introduces each module in written form and summarizes the main lessons learned at the end of each module.

### Technical specifications of CANreduce 3.0

CANreduce is a website accessed by an internet browser from a computer, tablet, or smartphone. The design automatically adapts to each device’s screen size (responsive design). While CANreduce 2.0 was based on Drupal 7, CANreduce 3.0 is based on Drupal 9. Drupal is an open source content management system that runs on PHP and MySQL/MariaDB. The website, including all data, runs on a litespeed webserver hosted by a professional company, and is located in a high-security data center in Switzerland. Physical access to this data center is only granted after biometric identification. All access via a browser is enforced through SSL encryptions. Participants have access to their account via their own username and password. The developers at the Principal Investigator’s (PI) institution have full access to all data from the participants (except their passwords) via personal administrator accounts. Data will be extracted at several time points (including a review of data quality) and stored at the PI's institution on local computers and local fileservers for analysis and archiving.

Participants can create an account by providing a username and e-mail-address. After clicking an e-mail verification link to ensure that the e-mail address they have entered is correct, they can create their password and start the baseline assessment procedure. All measurements in this study are entered via the website. Automatic input validation ensures a certain level of data quality. Sensitive data, like email addresses and phone numbers, will be deleted upon study completion.

### Safety

Potential risks to participants are assumed to be minimal. First, no drugs will be administered during the trial. Secondly, some people who might be at higher risk for adverse consequences are ineligible for the study (e.g., people with significant current suicidal thoughts). Thirdly, an instant help page will be available at all times that includes instructions on what participants might do if their life situation becomes unbearable (including emergency contacts). This instant help is mentioned explicitly at points in the program that might be particularly challenging for participants. It is expected, for example, that participants will experience some mild withdrawal symptoms — such as craving, mild depressive states, and sleep problems. These symptoms are mitigated by being explicitly addressed within the modules.

### Measures

Table 3  provides an overview of all measurements and when in the study they are used. All measurements are self-reported, assessed online, and detailed subsequently:*Sociodemographic data* include age, gender, sexual orientation, educational attainment, financial situation, and migration background.Problematic cannabis use is assessed with the revised version of the *Cannabis Use Disorders Identification Test (CUDIT-R* [68]*;)*. Each of the eight items contains a statement about cannabis use that must be answered on a 5-point Likert scale that ranges from "never" (0) to "daily or almost daily" (4). The total score ranges from 0 to 32 with scores of 8 or more indicating hazardous cannabis use and scores of 12 and more indicating a possible CUD.Various further aspects of cannabis use are assessed. Regarding *consumption patterns: (3a)* the i) number of years using cannabis, ii) means of consumption (oral, smoking or vaporizing), and iii) number of days using CBD over the last 30 days are measured. Participants then *define their personal standard joint (3b)* by selecting between i) indoor, outdoor, and resin, ii) mixed with or without tobacco, and iii) six different quantities of the substance, varying between 67 and 500 mg. Each of the resulting 36 combinations is illustrated with a photo of an unrolled joint paper on which the specific amount of cannabis (and tobacco) that has been selected by the participant is displayed. A ruler beside the unrolled joint serves as a reference. This standard joint is used as a quantitative unit to assess 3c) the frequency and quantity of cannabis use in the last seven days, in accordance with the *Time-Line-Follow-Back (TLFB)* method [69, 70].The *Severity of Dependence Scale (SDS)* is a five-item scale that can be used to screen for dependence. Each item must be answered on a 5-point Likert scale that ranges from 0 to 4. Total scores range from 0 to 20, with a score of 4 or more indicating cannabis dependence [71].The *short version of the Alcohol Use Disorders Identification Test (AUDIT-C* [72]*;)* is a screening tool with three items that assess problematic and risky alcohol consumption. All items must be answered on a 5-point-Likert scale, that ranges from 0 to 4. The total score ranges from 0 to 12, with scores of 3 (women) and 4 (men) indicating problematic use and scores of 4 (women) and 5 (men) or more indicating risky use.The *NIDA ASSIST* is an *Alcohol, Smoking and Substance Involvement Screening Test (ASSIST) from the National Institute on Drug Abuse (NIDA).* We only use the pre-screener [73] without the items on alcohol and tobacco. For each drug, consumption is rated, ranging from "never" (0) to "daily or almost daily" (4).Drug Abuse Screening Test (DAST-10) is an instrument with ten yes–no questions about drug abuse [74]. Each answer is allocated either 0 or 1 point, leading to a total score between 0 and 10. Scores are interpreted as follows: 0 for no problem, 1–2 for a low level, 3–5 for a moderate level, 6–8 for a substantial level, and 9–10 for a severe level of abuse.The *Perceived Stress Scale (PSS-10)* is an instrument with 10 statements about experiences of unpredictable, uncontrollable, and overwhelming life events. Answers range from "never" (0) to "very often" (4), leading to a total score between 0 to 40 with higher numbers indicating more stress, but without distinct any cut-offs for diagnostic purposes [75, 76].The *Patient Health Questionnaire for Depression (PHQ-9)* consists of nine items that assess degree of depression. Answers range from "not at all" (0) to "almost daily" (3), resulting in a total score between 0 and 27 [77]. A score of 10 or higher is considered indicative of a major depressive disorder [78].*The Generalized Anxiety Disorder Screener (GAD-7)* is a screener with seven items on anxiety symptoms, with answers ranging from "not at all" (0) to "almost daily" (3) and total scores between 0 and 21; any score of 10 or higher is considered indicative of a generalized anxiety disorder [79].The Adult ADHD Self-Report Scale (ASRS-V1.1) is a six-item questionnaire on attention deficit and hyperactivity, with answers ranging from "never (0) to "very often" (4), leading to a total score between 0 and 24 [80]. Total scores range from 0 to 24 with values of 14 and above indicating a positive screening result for ADHD [81].*The Mindfulness Attention Awareness Scale (MAAS)* is a questionnaire with 15 statements about everyday experiences in mindfulness, with answers ranging from "almost always" (1) to "almost never" (6), and higher mean scores indicating greater mindfulness [82, 83].*The Comprehensive Inventory of Mindfulness Experiences (CHIME)* is a 37-item questionnaire with answers ranging from "almost never" (1) to "almost always" (6), with higher mean scores representing more mindfulness. This relatively large instrument has eight subscales (inner awareness, outer awareness, acting with awareness, acceptance, decentering/non-reactivity, openness, relativity, and insight) and covers all aspects of mindfulness employed in current mindfulness scales [84].*Previous experience with meditation* is assessed with two questions about frequency (never, once, sometimes, regular) and guidance (innately learned, self-taught from books, learned in a course, guided by an app).*The Client Satisfaction Questionnaire for Internet Interventions (CSQ-I)* is specifically designed to assess client’s satisfaction with internet health interventions. It consists of eight items with answers ranging from "disagree" (1) to "agree" (4), leading to scores between 8 and 32; higher scores indicate higher levels of satisfaction [85].*Negative effects* of internet interventions are assessed according to Rozental [86]. Participants are asked if they have experienced any negative side effect that they attribute to the program. If so, they are asked to describe it and rate the severity of any resulting impairment.*Use of any services besides CANreduce*, like online counseling, drug counseling, general practitioner, psychologist, or psychiatrist. Participants are asked to respond ‘yes’ or ‘no’ to all of these services and to list any other unlisted services used.*Adherence and Retention:* Adherence is operationalized as average completion rate spanning the eight modules, with module completion rate defined as the highest page number visited divided by the highest page number available in a given module. Retention is operationalized as the average completion rate of the weekly consumption diary over the six-week program.

**Table 3 Tab3:** Overview of all measures and their measurement time points

	**Assessment instruments**	**Base-line (t**_**0**_**)**	**6 weeks (t**_**1**_**)**	**3 months follow-up (t**_**2**_**)**	**6 months follow-up (t**_**3**_**)**
1	Socio-demographics (age, gender, sexual orientation, educational attainment, migration background, financial situation)	X			
2	Cannabis Use Disorders Identification Test (CUDIT-R)	X	X	X	X
3	*Cannabis use*				
3a	Consumption Patterns (Years of Use, 30-day point prevalence of cannabis and CBD abstinence, Type of Consumption)	X	X	X	X
3b	Defining the personal standard joint	X			
3c	TLFB (Cannabis use frequency and amount for the last 7 days in standard joint units)	X	X	X	X
4	Severity of Dependence Scale (SDS)	X	X	X	X
5	Short version of the Alcohol Use Disorders Identification Test (AUDIT-C)	X		X	X
6	National Institute on Drug Abuse *Screening (NIDA ASSIST)*	X		X	X
7	Drug Abuse Screening Test (DAST-10)	X			
8	Perceived Stress Scale (PSS-10)	X	X	X	X
9	Patient Health Questionnaire for Depression (PHQ-9)	X		X	X
10	Generalized Anxiety Disorder Screener (GAD-7)	X		X	X
11	Adult ADHD Self-Report Scale (ASRS-V1.1)	X			
12	Mindfulness Attention Awareness Scale (MAAS)	X	X	X	X
13	Comprehensive Inventory of Mindfulness Experiences (CHIME)	X			
14	Previous experience in meditation (no official instrument)	X			
15	Client Satisfaction Questionnaire for Internet Interventions (CSQ-I)		X^a^		
16	Negative effects, according to Rozental et al. (2015)		X		
17	Use of any services besides CANreduce			X	X
18	Adherence and Retention^b^		X		

^a^ Only for study arms 1 and 2

^b^ Adherence and retention are constructs measured indirectly and not part of a questionnaire

The primary study outcome is the number of days of cannabis use over the preceding 30 days.

Secondary outcomes are quantity and frequency of cannabis use over the last seven days’; scores for the SDS, AUDIT-C, NIDA-ASSIST, PSS-10, PHQ-9, GAD-7, MAAS, and CSQ-I., and any negative effects attributed to the program.

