**Methods:**

This paper details the protocol for a three-arm randomized controlled trial comparing a mindfulness-based self-help IMI (arm 1) and cognitive-behavioral therapy (CBT)-based self-help IMI (arm 2) versus being on a waiting list (arm 3) in their effectiveness reducing cannabis use in frequent cannabis users. Predictors of retention, adherence and treatment outcomes will be identified and similarities between the two active intervention arms explored. Both active interventions last six weeks and consist of eight modules designed to reduce cannabis use and common mental health symptoms. With a targeted sample size of *n* = 210 per treatment arm, data will be collected at baseline immediately before program use is initiated; at six weeks, immediately after program completion; and at three and six months post baseline assessment to assess the retention of any gains achieved during treatment.

The primary outcome will be number of days of cannabis use over the preceding 30 days. Secondary outcomes will include further measures of cannabis use and use of other substances, changes in mental health symptoms and mindfulness, client satisfaction, intervention retention and adherence, and adverse effects. Data analysis will follow ITT principles and primarily employ (generalized) linear mixed models.

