### Data analyses

Data will be analyzed according to the ITT principle. Multiple imputation procedures, using the R package *mice* [87], will be used to address missing data. *mice* involves specifying a multivariate distribution for the missing data and drawing imputations from their conditional distributions by Markov chain Monte Carlo (MCMC) techniques. We intend to use 20 imputed data sets, as this has been deemed sufficient [87]. The imputation model will include all primary and secondary outcomes (see above). Adjunct variables, like sociodemographic data, will be included if they improve convergence within the imputation model.

Differences in primary and secondary continuous outcome variables between the two active study arms (1 and 2) at baseline and at both follow-up points will be tested using linear mixed models (LMM). The LMMs will be specified to model clusters and repeated measures by defining random effects for study condition and time (repeated measures). Appropriate distributions for non-normal continuous outcomes will be specified (e.g., negative binomial, zero-inflated). In addition to the ITT analyses, per-protocol analyses will be performed.

To investigate the exploratory research question of whether study arm 1 (mindfulness-based self-help IMI) results in a similar reduction in days of cannabis use as study arm 2 (CBT-based self-help IMI), a confidence interval approach will be used for the ES of the difference between these two study arms, using a two-sided 0.05 level of significance [54]. The equivalence margin is a priori set at d = 0.20, corresponding to the smallest value that would constitute a relevant effect [88]. The upper bound of the 95% CI for the ES will be compared against the predefined equivalence margin of d = 0.20 and must be below the margin to show equivalence.

Additional exploratory regression analyses will be conducted to determine whether baseline variables predict the frequency or quantity of cannabis use, severity of dependence (SDS), reduced psychiatric symptoms (PHQ-9, GAD-7), perceived stress (PSS-10) and mindfulness (MAAS) at 3 and/or 6 months follow-up, treatment retention, and adherence. For these analyses, we will use linear, multinomial, or binary regression models, depending on the scale used for the outcome measure. Treatment retention and client satisfaction will be compared between study arms one and two by Pearson chi-square analysis at week 6 (intervention end).

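### The abstract counts retention and adherence as secondary outcomes and the Measures list does not; because that list defines the imputation model, website usage data are left out on the literal reading, which can bias the comparisons with the waiting list

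*Protocol article*

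**What the plan says.** Four parts of the protocol article bear on this.

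- **Abstract, Methods.** The secondary outcomes include "client satisfaction, intervention retention and adherence, and adverse effects".
- **Measures, paragraph after Table 3.** The itemised list gives quantity and frequency of use over seven days and then "scores for the SDS, AUDIT-C, NIDA-ASSIST, PSS-10, PHQ-9, GAD-7, MAAS, and CSQ-I., and any negative effects attributed to the program". Retention and adherence are absent, although both are defined in the same section ("Adherence is operationalized as average completion rate spanning the eight modules"; retention is average weekly diary completion) and form row 18 of Table 3, marked at six weeks. Footnote b of the table says that they are measured indirectly and are not part of a questionnaire.
- **Data analyses, imputation.** "The imputation model will include all primary and secondary outcomes (see above". For anything else: "Adjunct variables, like sociodemographic data, will be included if they improve convergence within the imputation model".
- **Data analyses, comparisons.** "Treatment retention and client satisfaction will be compared between study arms one and two by Pearson chi-square analysis at week 6". Adherence appears only as a dependent variable in the exploratory regressions on baseline variables ("at 3 and/or 6 months follow-up, treatment retention, and adherence").

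Two further facts matter. Arm 3 waits six months for access (Assessments, compensation, and randomization), so it has no module or diary use. The Discussion expects relatively large drop-out and says that adherence may be limited, but gives no rate for either.

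**The concern.** The mismatch has a practical effect because the disputed list decides what goes into the imputation model. If the abstract governs, usage is in. If the Measures list governs, usage is out unless it happens to help convergence. Convergence is the wrong test for an auxiliary variable. A variable earns its place by predicting who is missing or what the missing value would have been, and a model can converge well without it.

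Usage is a natural candidate here. It is recorded without the participant answering a survey, so it exists for active-arm participants lost to follow-up. The Background also hypothesises that coaching raises adherence and effectiveness together, so the authors themselves regard the two as linked. If people who stop using the programme also skip follow-up and reduce their use less, imputing them from baseline and questionnaire data alone gives them outcomes closer to those of engaged responders. Arm 3 has no programme use, so this particular mechanism acts only in arms 1 and 2, and any resulting bias enters hypotheses 1 and 2.

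A separate gap is that an outcome named in the abstract has no stated comparison between the two programmes.

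**Working it through.** **Texts side by side.** The abstract includes retention and adherence, and the Measures list does not. The imputation sentence refers back to what stands above it, and the itemised list is the nearest definition in the body. The literal reading therefore leaves usage out. The clause on adjunct variables gives sociodemographic data only as an example, so it does not forbid usage; it ties entry to convergence.

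**Adherence comparison.** The chi-square sentence names retention and satisfaction. The general mixed model for continuous secondary outcomes compares arms 1 and 2 at baseline and the follow-ups, whereas adherence exists only at six weeks. Neither provides a comparison of adherence.

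**Size.** The plan gives no figure to reproduce on this point, and no drop-out rate or usage–outcome relation. Everything below rests on assumed parameters.

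In a large sample, the bias in an arm mean from omitting usage is about

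bias = (share missing) × (usage gap, responders minus drop-outs, in SD) × (outcome slope per SD of usage, given the variables already in the model).

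An illustration with 1,000,000 simulated participants per arm, usage present in arm 1 only and 50% follow-up in both arms gave the results below. The outcome is cannabis use, so negative is better. Usage slope is the effect of one SD of usage on the outcome. Stay slope is the log-odds of answering follow-up per SD of usage.

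| Usage slope | Stay slope | True d | Imputed from baseline | Baseline + 6-week outcome | Baseline + usage |
|---|---|---|---|---|---|
| −0.30 | +1.0 | −0.262 | −0.390 | −0.331 | −0.261 |
| −0.30 | +0.5 | −0.261 | −0.336 | −0.301 | −0.261 |
| −0.15 | +0.5 | −0.261 | −0.297 | −0.281 | −0.260 |
| −0.30 | 0 | −0.262 | −0.261 | −0.261 | −0.260 |
| 0 | +1.0 | −0.262 | −0.262 | −0.262 | −0.263 |
| −0.30 | −0.5 | −0.258 | −0.186 | −0.221 | −0.260 |
| +0.15 | +1.0 | −0.260 | −0.196 | −0.222 | −0.260 |

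Hand check of the first row: a stay slope of 1.0 gives a usage gap of 0.83 SD, and the outcome SD in arm 3 is √(0.5² + 0.32² + 0.75²) = 0.957. Then 0.5 × 0.83 × 0.30 / 0.957 = 0.130, against 0.390 − 0.262 = 0.128 in the table.

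Reading the table:
- Overstatement reaches 0.128 with baseline only and 0.331 − 0.262 = 0.069 once the 6-week outcome is used.
- Understatement reaches 0.258 − 0.186 = 0.072 and 0.258 − 0.221 = 0.037 respectively, when heavier users drop out more. The negative stay slope was run only to −0.5, so the smaller figure on this side partly reflects the range tried.
- There is no shift if usage is unrelated to outcome or to drop-out.
- With usage in the model, the true effect is recovered in every row.

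The 6-week outcome was treated as observed for everyone, which flatters the model without usage. If most drop-outs also miss week 6, the shift lies nearer the baseline-only column.

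**Scale.** With complete data, the standard error of d at 210 per arm is √(2/210) = 0.098. The equivalence margin is 0.20, and the Background quotes 0.11 for earlier digital interventions.

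**The case against.** The strongest reply is that this is a labelling mismatch between an abstract and a list, and that the full predictor list for the imputation is commonly left to an analysis plan, which is not shown. The second half is fair as far as it goes: the absence of a full list is not the complaint. The complaint is that the article does state a rule, that the rule points to a list the article contradicts, and that its criterion for further variables is the wrong one.

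Three stronger readings are tempting, and the documents do not support them.

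- A reader might infer that benefit will be overstated. No drop-out rate, usage–outcome relation or usage–drop-out relation is given, and the table shows the sign reversing or the bias vanishing. The planned model also holds more than the illustration does, with several cannabis and mental-health measures at week 6 that would absorb part of any bias. The figures further assume no imputation bias in arm 3, where people may drop out selectively for other reasons. Between arms 1 and 2, similar engagement would largely cancel the effect.
- A reader might infer that the short list is why adherence has no arm comparison. Retention is missing from the same list and is still tested, so the two gaps are separate.
- A reader might infer that completion rates are the only post-baseline data on people who answer no follow-up. The consumption diary also records joints actually smoked, for those who fill it in.

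Adding usage is also more than lengthening a list: arm 3 has no values, so it requires imputation by arm. At 50% follow-up that leaves 210 × 0.5 = 105 observed cases per arm, which limits the number of predictors.

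**Conclusion.** The point holds in a limited form. The abstract and the Measures list contradict each other on retention and adherence, the imputation model takes its content from that list, and the stated criterion for adding variables does not address bias from drop-out. On the literal reading, usage data already held for active-arm participants lost to follow-up are not used.

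This can bias arms 1 and 2 against arm 3, provided that usage relates to both drop-out and outcome beyond what is already in the model. Overstated benefit is the plausible direction, because it needs only that engaged users do better and stay longer. That is a judgement and not something the documents show. The illustrative shifts, from none to about d = 0.1 either way, rest on assumed slopes and 50% follow-up; they show what is possible and do not estimate the bias in this trial. The missing comparison of adherence between arms 1 and 2 is a separate and smaller gap. The change is worth making because it is cheap and, in the illustration, removed the bias whichever way it ran.

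**What to change.** 1. Make the abstract and the Measures list agree. If both measures are secondary outcomes, add adherence (average module completion) and retention (average diary completion) to the list, for arms 1 and 2. The same edit can settle the status of CUDIT-R, which is measured at all four time points and is also absent from the list.
2. In Data analyses, replace the convergence criterion with one that admits variables predicting missingness or the outcome. Name module completion and diary completion as predictors when imputing arms 1 and 2, and impute each arm separately because arm 3 has no usage.
3. State a week-6 comparison of adherence between arms 1 and 2, with a method suited to an average completion rate.

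The cost is some wording and a few lines of imputation code; no new data are needed. The downside is a few more predictors, so the predictor set per arm must be kept modest if drop-out is high. Reported effects may also come out slightly smaller.
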